### Recruitment

Recruitment occurs at each site through the use of flyers, email listserves, social media postings and vlogs (video-based blogs), and community outreach. Once a potential participant is deemed eligible, a research staff educates him or her on the study, and if interested in proceeding, an in-person research visit is scheduled. The informed consent is reviewed and signed at the in-person visit before proceeding with the study. The research staff who worked with the Deaf participants are fluent in ASL.

### Eligibility Criteria

To be eligible, study participants must be aged at least 18 years. For the Deaf study group, eligible Deaf participants must identify themselves as Deaf and communicate primarily in ASL. For the hearing comparison group, the hearing study participants also must be aged at least 18 years but self-report normal hearing and communicate in spoken English (ie, English monolinguals). Participants will be excluded if they have any cognitive impairments (eg, because of dementia, delirium, or intoxication), inability to consent to the study, or limited vision.

### Sample Size

To detect differences between correlations at 1% level of significance with 80% power, based on a one-sided Z-test of comparison of Fisher Z-transformed correlations, we plan to recruit 450 participants in each group that will allow us to detect a minimum difference of 20%. The sample size is more than adequate in detecting the differences between the groups with respect to the accessibility, acquisition, and attitude measures in aim 1 as well as to assess deafness as an effect modifier of the association between health literacy and ASK with health information.

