The ASL-NVS and the English-NVS will be used to assess the health literacy score in both Deaf and hearing participants, respectively. The health literacy indicator (ASL-NVS) ranges in value from 0 to 6. To understand whether the association between health literacy and ASK related to health information differs between Deaf and hearing individuals, we shall compute in the Deaf and hearing groups Fisher Z-transformed partial correlations between health literacy and each of the constructs, adjusted for the socioeconomic factors and potential site differences. Subsequently, 2-sample Z-test of these correlations will be carried out for each construct. We shall supplement this analysis with a regression approach where health literacy will be regressed on the group and each of the constructs along with their interaction controlling for the socioeconomic factors and site. Although the interaction term is of primary focus, such a model will provide an overall appraisal of the association between health literacy and various covariates. On the basis of PI’s previous work involving the ASL-NVS, one can alternatively characterize health literacy as a categorical variable with categories of adequate (NVS score of 5-6), indeterminate (2-4), and inadequate (0-1). As a secondary analysis, we will conduct an ordinal logistic regression with the categorical outcome of health literacy using the same covariates in the model as mentioned above.

### Analyses for Aim 3

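### The 450 per group is justified by a one-sided 1% test although aim 2 has no direction, and the 20% detectable difference holds only above a certain correlation

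*Protocol article*

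**What the plan says.** The Sample Size section sets the error rates with "To detect differences between correlations at 1% level of significance with 80% power". It gives the test and the number together, "based on a one-sided Z-test of comparison of Fisher Z-transformed correlations, we plan to recruit 450 participants in each group", a number "that will allow us to detect a minimum difference of 20" per cent. It gives neither the scale of that 20% nor the correlations assumed. The next sentence begins "The sample size is more than adequate in detecting the differences between the groups" and covers both the aim 1 group comparisons and the aim 2 assessment of effect modification.

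The Overview describes aim 2 as assessing hearing status as an effect modifier. Statistical Analyses for Aim 2 gives the purpose as "To understand whether the association between health literacy and ASK related to health information differs between Deaf and hearing individuals". It plans partial correlations in each group, a two-sample Z-test for each construct with no side stated, and a supplementary regression with a group-by-construct interaction. The article does not say, for any construct, which group should show the stronger association.

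**The concern.** There are two problems, both in what the article states.

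- **Sidedness.** A one-sided test can declare a difference in one direction only. A question about whether two correlations differ, with no predicted direction, calls for a two-sided test. The power statement therefore describes a test that does not answer the aim 2 question.
- **The 20%.** Power for comparing two correlations depends on the gap between their Fisher Z values. The same gap in r gives a smaller Z gap near zero than further out. A single percentage without a base correlation is therefore not a smallest detectable difference.

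At stake is what readers may take from the aim 2 results. If several constructs correlate weakly with health literacy, power for a 0.20 difference is below the advertised 80%. A reader relying on the power statement would then put too much weight on a null result.

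**Working it through.** **Inputs from the Sample Size section:** alpha 0.01, one-sided; power 0.80; 450 per group; difference 20%. **Assumption:** 20% means an absolute difference of 0.20 in r.

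**Formulas.** With n per group, SE = sqrt(2/(n − 3)) and Δ = atanh(r2) − atanh(r1).
- Detectable Δ = (z_alpha + z_power) × SE
- Power = Φ(Δ/SE − z_alpha)
- n per group = 2 × ((z_alpha + z_power)/Δ)² + 3

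**1. The plan's own figure.** The formula needs both correlations, so 450 cannot be reproduced from the stated inputs alone. Under one-sided 1% and 80% power, 0.10 vs 0.30 needs 462 per group and 0.15 vs 0.35 needs 441. For 0.13 vs 0.33, Δ = 0.3428 − 0.1307 = 0.2121 and n = 2 × (3.168/0.2121)² + 3 = 449.2, which rounds up to 450. The stated number is thus consistent with a lower correlation near 0.13.

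**2. What 450 detects under the stated test.** SE = sqrt(2/447) = 0.0669. Detectable Δ = (2.326 + 0.842) × 0.0669 = 0.212. A 0.20 gap in r reaches this only if the lower of two same-sign correlations is at least about 0.13.

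**3. Power with 450 per group for a 0.20 gap in r:**

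| Correlations | Δ | One-sided 1% | Two-sided 1% | Two-sided 5% |
|---|---|---|---|---|
| 0 vs 0.20 | 0.2027 | 75.9% | 67.5% | 85.8% |
| 0.10 vs 0.30 | 0.2092 | 78.8% | 70.9% | 87.9% |
| 0.20 vs 0.40 | 0.2209 | 83.6% | 76.6% | 91.0% |

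For 80% power, these pairs need 492, 462 and 415 per group at one-sided 1%, and 572, 537 and 482 at two-sided 1%.

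**4. Detectable difference with a two-sided test and 450 per group:**
- Two-sided 1%: (2.576 + 0.842) × 0.0669 = 0.229, for example 0 vs 0.225 or 0.2 vs 0.406. A 0.20 gap reaches 80% power only if the lower correlation is about 0.25 or more.
- Two-sided 5%: (1.960 + 0.842) × 0.0669 = 0.187, for example 0 vs 0.185. From 0.2, tanh(0.2027 + 0.1874) = 0.371.

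**5. Other readings of the 20%, under the stated one-sided 1% test.** As 0.20 on the Fisher Z scale, 80% power needs 505 per group, and 450 gives 74.7%. As a relative 20%, 0.50 vs 0.40 needs 1275 per group (power 32.7% with 450), while 0.70 vs 0.56 needs 369 (88.1%). No reading makes 20% a minimum that 450 per group reaches at every correlation.

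**6. Adjustment.** Aim 2 uses partial correlations. Assuming 10 covariates, n − 3 drops by 10 and one-sided 1% power becomes 74.9% (0 vs 0.20) and 82.6% (0.20 vs 0.40). This changes little.

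**The case against.** The strongest reply is that no arithmetic error has been shown. The 450 agrees with its stated inputs at an ordinary base correlation of about 0.13, and a journal article may leave that base value to the full protocol. Both points stand. But no base value turns 20% into a constant minimum, and none gives aim 2 a direction.

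A second reply is that one-sided 1% shares its critical value with two-sided 2%, so it is already stricter than a conventional two-sided 5% test. This also stands. The two-sided powers of 67% to 77% arise only if 1% is kept. The question requires two sides; it does not require 1%.

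Third, under the article's own test the shortfall near zero is small: about 0.21 detectable instead of 0.20. That is correct and limits the weight of the point.

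Two stronger readings are tempting, and the article does not support either:
- A reader might infer that differences in the unplanned direction will be discarded at analysis. One-sidedness appears only in the sizing. Statistical Analyses for Aim 2 states no side and adds an interaction regression, so no one-sided decision rule is fixed.
- A reader might infer that the whole adequacy sentence is wrong. It also covers aim 1, and nothing here counts against that. For a simple comparison of two means, 450 per group has 80% power for a standardised difference of about 3.168 × sqrt(2/450) = 0.21 at one-sided 1%.

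**Conclusion.** The concern holds in a limited form. The sizing test is one-sided for a question stated without direction, and the 20% is not a property of the design across correlations. Under the stated test, power for a 0.20 difference is 76% at 0 vs 0.20, passes 80% at a lower correlation of about 0.13, and is 84% at 0.20 vs 0.40.

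These figures assume that 20% is an absolute difference in r, that the two correlations have the same sign, and that all 450 per group contribute data.

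This is a mismatched and under-specified justification. It does not show a study that is clearly too small. Whether the claim of adequacy for effect modification stands depends on the alpha adopted with a two-sided test: at 5% it is supported for a 0.20 difference; at 1% it is not supported for lower correlations below about 0.25.

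**What to change.** Keep 450 per group and change the wording:

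1. State the test as two-sided in Sample Size, and say the same for the Z-tests in Statistical Analyses for Aim 2.
2. State the alpha chosen, and replace the 20% with the detectable Fisher Z difference and example pairs. At two-sided 1%: 0.229 (0 vs 0.225; 0.2 vs 0.406). At two-sided 5%: 0.187 (0 vs 0.185).
3. Qualify the adequacy claim for effect modification to match that alpha. If 1% is kept, say that a 0.20 difference has 80% power only when the lower correlation is about 0.25 or more. Leave the aim 1 part of the sentence as it is.

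The cost is rewording. If 1% is kept, the stated detectable difference also becomes slightly less favourable (0.229 instead of 0.212 on the Fisher Z scale).

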### Measures

The constructs outlined in the Deaf Health Literacy conceptual model will be measured through a collection of chosen tools (see Table 1). These tools were selected primarily because of their accessibility (prior use with past projects involving Deaf participants) and their key constructs that they measure. There were several tools that required translation and adaptation before they could be used in the study. A translation work group (TWG) was formed for this purpose. ASL is a language with its own rules of semantics and syntax similar to other languages.

**Table 1 table1:** Key variables and their measures.

Key variables		Measures	Defintion
**Attitudes**			
	Self-efficacy	One’s belief in one’s ability to succeed in specific situations.	Self-efficacy for information seeking [26].
**Skills**			
	Cognition	Ability to process information, metacognition, and behavioral regulation, which all are important for learning and social behavior	Kaufman Brief Intelligence Test, Second Edition (assesses nonverbal cognition), and the Color Trails Test (assesses executive function) [27] provide standard scores. Both have been used extensively in Deaf populations [28,29].
	Reading literacy	Level of reading proficiency	reading grade level from the Test of Silent Contextual Reading Fluency, Second Edition [30]. This instrument is visual and provides a suitable tool for both Deaf and hearing populations.
	Electronic health (eHealth) literacy	Ability to seek out, find, evaluate and appraise, integrate, and apply what is obtained in an electronic or Web-based environment to solving a health problem.	eHealth literacy Scale (validated measure of Web-based and eHealth literacy) [31]. Adapted further for the Deaf ASL^a^ users that includes whether Web-based information is accessible in ASL.
	Visualization of health information	Visualization patterns of the presented health information.	Actual through eye tracking software, which assesses the visualization of health-related information on 4 health topics [20,32].
**Knowledge**			
	Health knowledge	Knowledge of cardiovascular health.	Wagner et al’s cardiovascular health knowledge measure [33].
	Language fluency	Level of expressive and receptive language proficiency.	(1) ASL-SRT^b^ [34] and (2) Speaking Grammar Subtest of the Test of Adolescent and Adult Language, Third Edition [35]. Both will assess reception and expressive fluency in both ASL and spoken English. The ASL-SRT has been used extensively in Deaf populations [36,37].

^a^ASL: American Sign Language.

^b^ASL-SRT: American Sign Language Sentence Reproduction Test.

The shape, placement, and movement of hands as well as facial expressions and body movements all play important parts in conveying important information. There is no written form of ASL, so the use of *ASL gloss* is a way to keep note of how the ASL concepts should be signed to convey the meaning of the question or instructions accurately. Furthermore, the use of gloss has to do with the fact that the target language may not have equivalent words to represent the original language. The majority of the instruments were already available in ASL before the study’s funding, but there was translation and adaptation work needed for the following instruments: eHealth literacy Scale (eHEALS; 8 questions), Pew Research Center’s *Health Online Survey* questions related to online technology and information use (41 questions) [25], certain sociodemographic questions, cardiovascular knowledge assessment (25 questions), and self-efficacy instrument (3 questions).

The TWG consisted of the principal investigator (PI), a faculty experienced in translation of research instruments for Deaf individuals, 1 ASL interpreter skilled in medical terminology, and 3 native Deaf signers experienced with translation work. This translational workgroup approach was successful in the adaption of prior measures (eg, American Sign Language-Newest Vital Sign, ASL-NVS) [1]. All TWG team members are bilingually fluent in English and ASL, including expertise within their content area or translation work. Moreover, the team members have Deaf cultural issues as they are members of the Deaf community. The TWG members, including Deaf and hearing individuals, worked collaboratively in small groups to prepare, review, and perform quality checks. In addition to multiple intrateam reviews during the translation and filming process (videos used for internal reviews and back-translation steps), external reviewers, who were not members of the translation team, provided an added layer of review and validation to ensure the quality and integrity of the work. A final blind back-translation from the ASL videos back to the English text was done by 2 bilingual Deaf experts (not involved with the TWG) to ensure translation accuracy. The above steps, including selection of the team, were done to establish appropriate language and cultural translations.

#### Health Literacy Assessment

The study will use an accessible and validated health literacy instrument for Deaf individuals that the PI derived from the Newest Vital Sign (referred to as the ASL-NVS) [38]. The ASL-NVS also offers other benefits as it assesses numeracy and reading literacy, has a short administration time with only 6 questions, and has been created and validated for other languages (eg, Spanish). The ASL-NVS is the first, and currently only, health literacy instrument available for the Deaf population. The instrument is available online [39].

#### Attitudes Assessment

##### Self-Efficacy

The *Self-efficacy for Information Seeking* scale is based on a scaled 3-item questionnaire assessing beliefs about ability to effectively perform specific information-related behaviors, such as finding information about health, evaluating the accuracy of health information, and using the internet to find information [26].

#### Skills Assessments

##### Nonverbal Cognitive Ability

The *Kaufman Brief Intelligence Test, Second Edition* (KBIT2) [40], Matrices Subtest (nonverbal intelligence quotient [IQ]) is computed based on one’s performance on a single multiple-choice subtest that does not require language skills. There are 46 items composed of several types of items involving visual stimuli, both meaningful (people and objects) and abstract (designs and symbols). All items require understanding of relationships among the stimuli and require the participant to point to the correct response. The KBIT2 nonverbal IQ has a 0.82 correlation with the Wechsler Adult Intelligence Scale, Third Edition, nonverbal composite [40]. This test has recently become commonly used in cognitive science and psycholinguistic studies that have included Deaf participants [21,22,29] to control for individual cognitive differences.

##### Executive Function Ability

The *Color Trails Test* (CTT) [27] is a measure of executive function abilities where participants are asked to rapidly connect numbered circles in sequence by alternating between pink and yellow circles [27]. The time to complete the task is recorded. The CTT has a test-retest reliability of 0.79 and has good factorial and criterion-related validity [27] with individuals with frontal lobe injuries. One of the coinvestigators ([name]) has used this test in cognitive science studies involving Deaf participants [28,29].

##### Reading Literacy

This will be assessed through the Test of Silent Contextual Reading Fluency, Second Edition [30]. This tool provides an efficient standardized literacy assessment for both Deaf and hearing participants.

##### Electronic Health Literacy

*eHEALS* was adapted to make it more culturally and linguistically appropriate for Deaf ASL users. The 8-item questionnaire inquires about the participants’ knowledge, comfort, and perceived skills at finding, evaluating, and applying eHealth information to health problems [31]. An additional 41 questions derived from the Pew Research Center’s *Health Online Survey* [25] related to online technology and information will assess the participant’s level of information access and use. This also was expanded to inquire about ownership of computer and mobile-based devices.

##### Health Information Evaluation Skill

Actual behaviors will be assessed for each participant through the use of the eye tracking software (Tobii; Tobii Technology) on 4 standardized health topic pages (2 with a picture and 2 without a picture). Eye tracking technology will be used to observe their ability to visualize and understand standardized health information with and without pictures. For eye tracking, we will use the Tobii eye tracker and software for data collection on fixation duration and fixation count on the presented information and the visualization pattern on both websites. This eye tracker provides extremely detailed eye tracking metrics (in milliseconds), including fixation counts, visit duration, time to first fixation, and percentage of viewing time fixated/clicked on a certain area of interest. It also can be used in either static (eg, print) or dynamic (eg, video or website scrolling) to assess each participant’s areas of interest.

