**Methods:**

This is an exploratory mixed methods study to identify predictors and moderators of health literacy in the Deaf population. These predictors of health literacy will be used to inform the second step that qualitatively explains the findings, including how Deaf individuals access and understand Web-based health information. Multiple interviewer- and computer-based instruments underwent translation and adaptation, from English to ASL, to make them accessible for the Deaf participants in our study. A planned sample of 450 Deaf ASL users and 450 hearing native English speakers, aged 18 to 70 years, will be recruited from 3 partnering sites: Rochester, NY; Flint, MI; and Chicago, IL. These individuals will participate in a single data collection visit. A subset of participants (approximately 30) with key characteristics of interest will be invited for a second data collection visit to observe and inquire more about their ability to directly access, navigate, and comprehend Web-based health information. The study will help assess how the ways health literacy and information are visualized may differ between Deaf individuals and hearing individuals. The study will also survey participants’ ownership and use of computer and mobile devices and their level of Web-based information use, including health information.

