## Introduction

### Background

Deaf American Sign Language (ASL) users are nearly 7 times more likely than their hearing peers to have inadequate health literacy [1]. Deaf ASL users (henceforth, Deaf) rarely receive language concordant health care services and are at highest risk for miscommunication with their health care providers. Deaf individuals understand less than 30% of what is being said through lipreading [2,3]. Furthermore, prose literacy poses a challenge for Deaf individuals; the average Deaf individual reads English at the fifth- to sixth-grade level [1,4-7]. The use of interpreters is the standard of care for Deaf ASL users, yet they are infrequently provided [8]. The majority of Deaf individuals (approximately 95%) have hearing family members who do not sign. Thus, many experience the *dinner table* syndrome, where they have encountered years at the dinner table watching close family members and friends converse with each other while being unable to understand what is being said, depriving them of incidental learning opportunities that many hearing individuals take for granted [9]. The loss of incidental learning opportunities and information marginalization for Deaf individuals occurs daily in a broad range of work, schools, friends, families, government, media, and health care contexts [1]. Many Deaf ASL users learn language, health information, and even culture via peers rather than family [10] and struggle to identify and correct misinformation [11]. Due to this communication-depleted milieu, inadequate health literacy may be an important cause of the lower level of health-related knowledge and worse health outcomes that have been observed among Deaf individuals.

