Frequency statistics will be used to summarize categorical data, whereas means (SDs) were computed to describe continuous data. Correlations between main study variables will also be analyzed using Pearson r correlation coefficients. Differences between the Deaf and hearing participants in terms of ASK related to health information will be assessed using linear regression models. To control for the effects of demographic and physiological covariates on the dependent variables of ASK related to health information, sociodemographic (eg, race) and physiological factors (ie, hearing loss severity and laterality) will be entered in model 1 as potential confounding factors affecting each variable of interest. As we are primarily interested in the additional effects of ASK related to health information on health literacy and eHealth, predictor variables will be subsequently entered in model 2. Differences between the Deaf and hearing participants in terms of ASK related to health information will be assessed using linear regression models. The scales for each modality described in Table 1 will be used as a separate outcome with Deaf versus hearing as the primary covariate. A propensity-adjusted analysis will also be conducted with the propensities defined as the predicted probability of having adequate health literacy as a function of sociodemographic factors estimated through a logistic regression model. For observational data, the propensity-matched methods are often deemed to be a better alternative to the usual multiple linear regression controlling for potential confounders. Strata based on propensity quantiles will be used as a categorical covariate in the linear regression model. Furthermore, the variability across sites will be controlled for in the model. Usual model diagnostics will be performed, followed by corrective actions as necessary.

### Statistical Analyses for Aim 2

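### The Aim 1 eye-tracking contrast between Deaf and hearing participants has no reading-adjusted companion, so on its own it cannot show that the groups visualize health information differently

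*Protocol article*

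**What the plan says.** Under Health Information Evaluation Skill, participants are assessed "on 4 standardized health topic pages (2 with a picture and 2 without a picture"). The stated purpose is this: "Eye tracking technology will be used to observe their ability to visualize and understand standardized health information with and without pictures". The planned data are "data collection on fixation duration and fixation count on the presented information and the visualization pattern on both websites". Neither the language of the pages nor the amount of text on them is given.

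Table 1 lists visualization of health information among the Skills variables, measured as follows: "Actual through eye tracking software, which assesses the visualization of health-related information on 4 health topics". Statistical Analyses for Aim 1 then states: "The scales for each modality described in Table 1 will be used as a separate outcome with Deaf versus hearing as the primary covariate". The adjusters named there are sociodemographic factors (race is the only example), severity and laterality of hearing loss, study site, and strata of a propensity score estimated from sociodemographic factors. Attitude, skill and knowledge variables, which include reading, enter in a second model step, but the text ties that step to health literacy and eHealth.

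Reading is measured in both groups with the Test of Silent Contextual Reading Fluency, Second Edition (TOSCRF-2), described as suitable for Deaf and hearing people alike. The Background section reports that "the average Deaf individual reads English at the fifth- to sixth-grade level". The hearing comparators are English monolinguals (Eligibility Criteria). The Abstract announces the comparison: "The study will help assess how the ways health literacy and information are visualized may differ between Deaf individuals and hearing individuals".

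**The concern.** Eye-tracking measures on a page of text may depend on how fluently the viewer reads that text. The document itself reports a low average English reading level among Deaf people and compares them with native English speakers. If the pages are in English, a Deaf-hearing difference in fixation count or duration could arise from a different way of taking in health information, from less fluent reading of English, or from both. The planned model does not tell these apart.

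The distinction matters for what the study wants to say. The Results section promises guidance that draws on visual learning skills and helps website editors. A difference in visual strategy points towards page layout and imagery. A difference in reading points towards simpler English or ASL content. The variable that would help separate the two is already collected in both groups on one scale.

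**Working it through.** **1. Is visualization a between-group outcome?** Yes. It is a Table 1 Skills variable, and the Aim 1 section makes each Table 1 scale an outcome with hearing group as the main covariate.

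**2. Is reading among the named adjusters for it?** No. Neither the confounder list, nor the propensity model, nor the site term includes reading. The model step that brings in skills variables is described for health literacy and eHealth. Reading is itself an Aim 1 outcome.

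**3. Are the pages in English?** Probably, but this is an inference. In favour: the comparators are monolingual in English, the pages are called standardized, and for ASL, "There is no written form of ASL". Against certainty: the pages are absent from the list of materials needing translation, but that list covers only what still had to be translated, and the same paragraph says most instruments already existed in ASL. If Deaf participants saw signed material instead, the two groups viewed different stimuli, and the contrast would need a different caveat.

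**4. Can the reading contribution be computed?** No. The document gives no SD for reading, no reading level for the hearing group, and no association between reading and fixation measures. The only sample-size calculation concerns comparing correlations and has no bearing here; only the 450 per group is taken from it.

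**5. Illustration under assumptions.** Let g be the reading gap between groups in within-group SDs, and b the SD change in the eye-tracking measure per SD of reading. Assume no direct group effect and ignore all planned covariates.
- Expected difference: d = g × b
- Standard error: √(2/450) = 0.0667 SD
- Chance of a significant result in the direction of d at two-sided 5%: Φ(d/0.0667 − 1.96)

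| g | b | d | d/SE | Chance |
|---|---|---|---|---|
| 0.5 | 0.1 | 0.05 | 0.75 | 11% |
| 0.5 | 0.2 | 0.10 | 1.5 | 32% |
| 1.0 | 0.1 | 0.10 | 1.5 | 32% |
| 1.0 | 0.2 | 0.20 | 3.0 | 85% |
| 1.0 | 0.3 | 0.30 | 4.5 | 99% |

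If g or b is zero, the chance is the nominal 5% (both directions). The spread comes from the assumed g and b, not from anything in the document. It shows only that 450 per group is enough for a modest reading effect to register. Adding the reading score would bring the rate back to about 5% under these same assumptions, provided reading is measured without error.

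**The case against.** **The planned contrast is not wrong.** Reading may lie on the path from deafness to how a page is viewed. The contrast without reading is then a valid total difference, and a significant result would be a real difference, not a false positive. The measured construct also covers understanding as well as visual strategy. This stands. A reader might infer that the plan's estimate is biased and must be replaced by an adjusted one; the document does not support that.

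**The premises are inferred.** The page language is not stated, the link between reading and fixation is not documented, and it is not said whether viewing is self-paced or timed. A reader might infer that a reading gap is bound to show up as a visualization difference. That is too strong: it needs both a gap in this sample and an association with the eye-tracking measure, and neither is quantified. Sociodemographic adjustment could remove part of any gap if it includes education. This also stands.

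**Other parts of the design address the reasons.** There are pages with and without pictures, and Aim 3 explores how and why participants act as they do. This stands only in part. No group-by-picture contrast is described for Aim 1, and adding a picture does not by itself remove the text. Aim 3 is a small qualitative sample carrying out live web searches on clinical vignettes, not viewing the standardized pages. Neither gives a quantitative separation of reading from visualization.

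**It could be left to the analysis plan.** An extra sensitivity model often is. Here, however, the article itself sets out which adjusters apply to the Aim 1 outcomes, and reading is not among them.

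**Conclusion.** The concern holds as a limit on interpretation. The planned contrast estimates the total Deaf-hearing difference in eye-tracking measures. If the pages carry English text, that difference may partly or wholly reflect English reading fluency, so on its own it cannot support a conclusion that the groups visualize health information differently. The size of the reading contribution is unknown; the percentages above are illustrations and should not be read as an expected error rate. The conclusion rests on two things the document makes plausible but does not establish: English text on the pages, and some dependence of the eye-tracking measures on reading skill. It is a worthwhile, inexpensive improvement rather than an error in the plan.

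**What to change.** State the language of the four pages. Keep the planned contrast and label it the total difference. For each eye-tracking outcome, add a second model that also includes the TOSCRF-2 score, and label its group coefficient a reading-adjusted (direct-effect) estimate. Report both, and word conclusions about visualization pattern in light of both. Persistence after adjustment should not be treated as proof of a different visual strategy, because measurement error in a single fluency score leaves some reading effect behind.

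The share of viewing time in an area of interest, which the article lists among the tracker's metrics, may be reported as supporting evidence. It is not free of reading speed, since a slower reader may also spend a larger share of time on text, so it should not replace the adjusted model.

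Cost: one extra model per outcome on data already collected, and a somewhat less precise group coefficient. With equal groups the variance inflation is 1 + g²/4. At g = 0.5 it is 1.0625 (standard error up about 3%), and at g = 1.0 it is 1.25 (up about 12%), before any gain from lower residual variance.
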